# The effect of high-intensity interval training on cognitive function in patients with substance use disorder: Study protocol for a two-armed randomized controlled trial

**DOI:** 10.3389/fspor.2022.954561

**Published:** 2022-12-09

**Keywords:** physical activity, exercise, high-intensity interval training (HIIT), maximal oxygen uptake, cognitive function, executive function, BRIEF-A, substance use disorder (SUD)

## Abstract

**Introduction:**

Substance use disorder (SUD) is characterized by cognitive impairment, especially executive dysfunction. Executive function is recognized as an important determinant of treatment outcome as it is associated with dropout rate, attendance to therapy and potential relapse after treatment termination. Physical activity can have beneficial effects on cognitive function, but there is still a lack of knowledge regarding potential benefits of aerobic exercise for executive function in SUD treatment. The aim of this study is to examine the effect of aerobic high-intensity interval training (HIIT) on cognitive function and the subsequent effect on treatment outcome in patients with SUD.

**Methods and analysis:**

This study is a randomized controlled trial, including men and women ≥18 years with diagnosed SUD by ICD-10. The patients will be recruited from the department for inpatient treatment at Blue Cross - Lade Addiction Treatment Center, Trondheim, Norway. Participants will be randomized 1:1 into either HIIT (3x/week) + treatment as usual (TAU), or TAU alone. Study outcomes will be assessed at baseline, after eight weeks of intervention, and at 3- and 12-months follow-up. The primary outcome is to compare the change in executive function (via altered BRIEF-A score, Behavior Rating Inventory of Executive Function-Adult) measured between the two study groups after eight weeks. Secondary outcomes include mapping of cognitive function in different subgroups (e.g. type of substance, age, fitness level), collecting self-reported information about quality of life, craving, sleep quality, etc., as well as assessing compliance to TAU and long-term treatment outcome.

**Ethics and dissemination:**

The project was approved by the Regional Ethical Committee and will be performed in accordance with this protocol and the Declaration of Helsinki. Written informed consent will be obtained from all participants prior to inclusion. This project will explore a novel approach to how exercise can be applied in SUD treatment, beyond the well-known effects on physical health. We expect to achieve new knowledge in regard to what extent HIIT can improve cognitive abilities and subsequent treatment outcome in SUD.

**Trial registration number:**

https://www.clinicaltrials.gov/NCT05324085.

## Introduction

1.

Substance use can have detrimental effects on a person's health and way of life, with negative consequences for family, friends, and participation in society. Substance use disorder (SUD) is a general term relating to harmful substance use that has evolved into abuse and addiction, and is covered by the diagnostic criteria ICD-10 and DSM-5, encompassing both illicit and licit substance use (1). According to the World Drug Report from 2021, about 275 million people worldwide used illicit drugs in 2019, whereof roughly 36 million individuals suffered from SUD (2). Almost eight times as many people (283 million) were registered having a SUD due to alcohol in 2016 (3). Patients with SUD also have high occurrence of both physical and mental comorbidities, leading to a reduced life expectancy of about 18–24 years – the most severe premature mortality gap among individuals with mental diseases (4).

A common feature in patients with SUD is impaired cognitive functioning (CF) (5–7). This particularly relates to executive functions, which for instance include decision-making, consequence analysis, impulse/self-control, and working memory (8, 9). Executive functioning is recognized as an important determinant of treatment outcome as it is associated with dropout rate, attendance to therapy sessions, and potential relapse after treatment termination (10–12). In this regard, Andersson et al. (2019) reported a relapse rate of approximately 40% three to six months after inpatient treatment in Norway (13). This constitutes a major concern and calls for new measures to overcome this challenge. Moreover, a certain degree of CF is required to benefit from verbal-based therapy forms and to learn new coping strategies, both of which are important components of SUD treatment (11). Impaired CF can not only negatively affect the treatment process itself, but also its long-term implications as for instance community integration, occupational functioning, and quality of life (14). Thus, improving CF could work as a primer for other treatment forms (e.g., psychotherapy), favoring the rehabilitation process and outcome acutely and long-term.

Physical activity (PA) can have beneficial effects on mental health and CF in healthy populations (15–17), and individuals with mental diseases (18–21), among them also patients with SUD (22, 23). A systematic review from the American College of Sports Medicine found strong evidence supporting that PA can improve CF, particularly in individuals with cognitive impairment (21). In line with this, several studies have shown that acute exercise (i.e., one single session) could improve CF in healthy individuals, an effect that was most pronounced after high-intensity aerobic exercise (24–26). Although few randomized controlled trials (RCTs) have been conducted, one RCT showed that 24 weeks of aerobic exercise improved executive function and cerebral cortical thickness in a healthy population aged 20–67 (15). Moreover, Hwang et al. (2018) reported healthy individuals with higher levels of aerobic capacity (measured as maximal oxygen uptake (V˙O_2max_)) performing better on neurocognitive tests than less fit individuals (27). Hence, these studies indicate that PA and exercise-induced fitness gains might contribute to improve CF.

Several physiological processes and biomarkers could be involved in improving CF. At the molecular level for instance, studies have suggested that brain-derived neurotrophic factor (BDNF) (28, 29), insulin-like growth factor 1 (IGF-1) and vascular endothelial growth factor (VEGF) (29, 30), blood lactate (29, 31, 32), fibronectin type III domain-containing protein 5/Irisin (33), Klotho (34), glycosylphosphatidylinositol (GPI)-specific phospholipase D1 (Gpld1) (35), and interleukin 6 (IL-6) (36, 37) are potential candidates favoring cognition, memory and learning. Insulin and glucose metabolism are other possible links, suggesting that improved insulin sensitivity and glucose handling by PA influence brain function and cognitive abilities (38, 39). Finally, fitness status (i.e., V˙O_2max_) correlated with cerebral blood flow velocity and vasomotor reactivity, and constituted a determinant of cognitive abilities (27). Those are promising findings, but the biological mechanisms underpinning the effect of exercise on CFs are still poorly understood, and warrant further exploration (40). Thus, analyzing relevant biomarkers could contribute to new knowledge to what extent they can act as physiological mediators between exercise and improved CF.

As a measure to improve somatic health in patients with SUD, aerobic high-intensity interval training (HIIT) has been implemented as mandatory part of treatment in several inpatient clinics in Norway. Aerobic HIIT has been shown to be particularly effective for improving cardiorespiratory fitness and cardiometabolic health, also in SUD inpatients (41). Additionally, higher levels of aerobic fitness have been linked to better performance on neurocognitive tests (27), and both studies with acute (24–26, 42) and chronic HIIT interventions (43) showed promising effects on CF. Since cognitive difficulties remain a critical obstacle for recovery and community integration in patients with SUD, exercise as adjunct therapy could play a vital role in restoring cognitive resources and improve treatment outcome. However, there is still a lack of RCTs examining the effects of specific training regimes on CF in this patient group, and whether such improvements can benefit other parts of the treatment. Altogether, aerobic HIIT seems to be an appropriate intervention for concurrent improvements in physical and mental health in patients with SUD.

This project will examine a novel approach to how structured exercise can be applied in SUD treatment and could add to develop new non-pharmacological treatment options. The socioeconomic burden related to substance abuse is high (44, 45), and this study may also contribute to decrease health care costs by improving the outcome of clinical treatment and integration into society. In addition, it may contribute to improved individual health and well-being among these patients. Knowledge from this trial may, therefore, provide guidance on how supervised exercise can be used as a cost-effective and holistic approach to SUD treatment encompassing both somatic and mental health, with improved quality of life as the ultimate goal. This protocol describes the study's design, aims, methodology and clinical significance.

**Aim**

The overall aim of this project is to investigate the effect of HIIT on CF and associated mechanisms, and the subsequent effect on treatment outcome in patients with SUD.

*Primary aim*
•Assess the change in executive function between an intervention group (HIIT + treatment as usual (TAU)) and a control group (TAU) after eight weeks of intervention. Executive function will be assessed using the neuropsychological test BRIEF-A (Behavior Rating Inventory of Executive Function-Adult, self-report version). This test has been established as a valid and reliable assessment of executive functions in patients with SUD (5, 6), and was therefore chosen as the primary endpoint of this study.*Secondary aims*
•Map CF in subgroups of patients with SUD (e.g. type of substance, age, fitness level).•Change in other neuropsychological assessments (i.e. Montreal Cognitive Assessment (MoCA), Stroop test, working memory tasks) between time points (Table 1).•Change in scores on self-report questionnaires (e.g. substance use, mental distress, sleep quality, quality of life, etc.) between time points (Table 1).•Assess compliance to TAU (e.g. therapeutic hours) and long-term outcome at follow-up (i.e. relapse rate).•Analyze exercise-induced responses of neurocognitive biochemical markers.

**Table 1 T1:** Overview of time points of measurements.

	Pre-intervention	Intervention (eight weeks)	Post-intervention	3-months follow-up	12-months follow-up
Demographic information	x				
Patient journal*	x		x		
Concomitant medications	x	x	x		
Adverse events		x			
Physical examination/test	x		x		
– Anthropometrics – Blood sample – V˙O_2max_-test					
Neuropsychological tests					
– BRIEF-A – MoCA – Stroop test – Working memory tasks	x		x	x	x
	x		x		
	x		x		
	x		x		
Questionnaires					
– Substance use, mental distress, sleep quality, quality of life	x		x	x	x
– IPAQ	x		x		

* SUD diagnosis (i.e. primary substance of use), comorbidities and therapeutic hours. SUD, Substance use disorder; V˙O_2max_, Maximal oxygen uptake; BRIEF-A, Behavior rating inventory of executive function-adult; MoCA, Montreal cognitive assessment; IPAQ, International physical activity questionnaire.

## Materials and methods

2.

### Study design and participants

2.1.

This study is a parallel-group RCT (superiority trial) initiated and coordinated by the Clinic of Substance Use and Addiction Medicine (CSAM), St. Olavs Hospital, Trondheim, Norway. Patients with SUD will be recruited from the department for inpatient treatment at Blue Cross - Lade Addiction Treatment Center (Lade ATC), Trondheim, Norway (inclusion and exclusion criteria see Figure 1). Eligible patients will be stratified for primary substance of use (i.e., alcohol or other) and randomized 1:1 to either aerobic HIIT + TAU, or TAU alone (Figure 2). The Clinical Research Unit of Central Norway will provide a block randomization with the software WebCRF3. Recruitment and testing of participants will be carried out by research staff affiliated CSAM, as will the supervision of the HIIT exercise sessions. Therapists and research staff at Lade ATC will inform the patients about the study after an initial detoxification phase. The research staff will then schedule to meet with the patient to provide detailed information, and schedule baseline assessments as soon as the patient has agreed to participate and has signed the written consent form. All testing and training sessions will be performed on-site at Lade ATC. Most patients are hospitalized for 8–12 weeks and will, thus, be recruited for eight weeks. Also, eight weeks of HIIT have been shown to significantly improve aerobic fitness in patients with SUD (41), and to improve executive function in healthy individuals (43).

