##### BRIEF-A

2.2.1.1.

The BRIEF-A is a 75-item standardized questionnaire appraising executive functions in real-life situations (48). It incorporates self-reported cognitive characteristics and collects subjective information about the ability to maintain appropriate control of emotional responses and behavior. The BRIEF-A encompasses nine sub-scales in three indexes/composite scores: *inhibit, shift, self-monitor, emotional control* (Behavioral Regulation Index, BRI); *initiate, plan/organize, working memory, organization of materials, and task monitor* (Metacognition Index, MI); BRI and MI are also combined to an overall summary score (Global Executive Composite, GEC). It additionally includes three validity scales (i.e., negativity, inconsistency, and infrequency). Conducting BRIEF-A takes 10–15 min. All items are rated with a 3-point scale, whereas a total score ≥65 points is considered as a clinically significant executive function deficiency (48, 49). The BRIEF-A has been shown to be particularly sensitive for assessing executive functions in the SUD population, and is considered more relevant for real-life situations than performance-oriented measures of executive functions (e.g., memory tasks) (5, 50).

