##### MoCA

2.2.1.2.

The MoCA is a brief screening tool to detect mild cognitive impairment (51), and is used in populations with different mental and cognitive health challenges, including SUD (6, 52). It is a performance-based test that can be administered in approximately ten minutes and assesses the following CF categories: *visuospatial/executive abilities*, *naming*, *memory*, *attention*, *language*, *abstraction*, and *orientation* (51). All categories range from 3 to 5 points each, leading to a maximal score of 30 points, whereas a score of <26 points is considered as having impaired CF (51).

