#### Control group

2.3.1.

Participants will receive standard TAU by therapists at Lade ATC with specific competence in working with patients with SUD. The content of TAU is broadly individualized, but also includes various forms of group therapy, psychotherapy, psychoeducation and PA. The PA schedule for the patients typically includes gym-based exercises (e.g., yoga, different types of circuit training, team sports) and various outdoor activities (e.g., walks, hikes, bonfire), four times per week all together.

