#### Exercise group

2.3.2.

Participants will undergo eight weeks of supervised aerobic HIIT, three times a week. This type of training is chosen since it earlier has been shown to be effective for improving somatic health in patients with SUD (41), and to have promising effects on CF as well (43, 75). The HIIT sessions will substitute most of the PA sessions included in TAU, and will be performed as 4 × 4 min intervals, running (or walking on steep incline) on a treadmill (see Figure 3 for illustration). The session will start with a 10-min warm-up at 60%–70% of HR_max_, followed by 4 × 4-min intervals at ∼90% of HR_max_, with 3-min active rest periods at approximately 60%–70% of HR_max_ between each interval, as described previously (41). The workload is relative to the maximal exercise capacity of each patient, and will be controlled using HR monitors (Polar Vantage M multisport watch and HR sensor H10, Polar Electro, Finland) and Borg scale derived RPE (60). We will instruct the participants to follow a RPE score of 16–18 (hard–very hard) for the interval period and 11–13 (fairly light–somewhat hard) for the warm-up, active rest periods, and cool-down. Total duration of each HIIT session is approximately 40–45 min.

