### Blinding

2.6.

Due to the nature of the study being an interventional trial with supervised training sessions, the study investigators and participants will not be blinded to group allocation. However, we will undertake baseline assessments prior to randomization.

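### The team that supervises the HIIT sessions also runs the week-8 tests, unblinded, so the testers may have a training relationship with one arm only

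*Protocol article*

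**What the plan says.** Section 2.1 (Study design and participants) of the protocol article names one team for three jobs: "Recruitment and testing of participants will be carried out by research staff affiliated CSAM, as will the supervision of the HIIT exercise sessions".

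Section 2.6 (Blinding) says that "the study investigators and participants will not be blinded to group allocation" and gives the supervised training as the reason. It offers one safeguard: "However, we will undertake baseline assessments prior to randomization".

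The two arms differ in who treats them. In section 2.3.2 (Exercise group), "Participants will undergo eight weeks of supervised aerobic HIIT, three times a week". In section 2.3.1 (Control group), "Participants will receive standard TAU by therapists at Lade ATC with specific competence in working with patients with SUD".

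Three outcomes depend on the patient's own rating, on an examiner or on effort:
- The primary outcome is a self-rating. The Aim states: "Executive function will be assessed using the neuropsychological test BRIEF-A (Behavior Rating Inventory of Executive Function-Adult, self-report version". Table 1 schedules it at all four assessment times.
- Of the MoCA, section 2.2.1.2 says: "It is a performance-based test that can be administered in approximately ten minutes". Table 1 schedules it before and after the intervention.
- The treadmill test (section 2.2.2.2) is individualised, with the workload stepped up until the patient is exhausted.

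**The concern.** Supervised training explains why patients and trainers cannot be blinded. It does not explain why the training team should also collect the outcomes. Measuring baseline before randomization protects the baseline only; the primary comparison is made at week 8.

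By then, HIIT patients may have spent eight weeks being coached by members of the team that tests them, and control patients have not. The overlap could act in three ways:
- A patient who rates their own everyday functioning for a team that has coached them may lean toward a favourable answer.
- An examiner who knows the allocation may administer the MoCA a little differently.
- Encouragement on the treadmill may differ between arms.

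All three would most plausibly favour HIIT. A bias of this kind does not shrink as more patients are recruited. The conclusion on executive function is what is at stake.

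**Working it through.** **1. Who meets whom by week 8**

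| | HIIT + TAU | TAU alone |
|---|---|---|
| Recruited and tested by | CSAM research staff (2.1) | CSAM research staff (2.1) |
| HIIT supervised by | CSAM research staff (2.1) | not applicable |
| TAU delivered by | Lade ATC therapists | Lade ATC therapists (2.3.1) |
| HIIT sessions supervised by the testing team | up to 3 x 8 = 24 | 0 |

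Section 2.5 also counts 24 sessions, in its per-protocol threshold of 17 out of 24. The article does not separate the two roles within the CSAM team and names no independent tester for week 8.

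**2. Which measures are exposed**

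- More exposed: the BRIEF-A and questionnaires (self-report), the MoCA (administered) and the treadmill test (effort-dependent).
- Less exposed: the Stroop and working memory tasks, which are computer-based and adapt to performance automatically (2.2.1.3), and the blood samples, which Lade ATC staff draw (2.2.2.3).
- In between: the treadmill result has verification criteria (oxygen uptake plateau, respiratory exchange ratio above 1.05, or lactate above 7 mmol). These limit encouragement effects without removing them.

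**3. The plan's own sample size, as the reference scale**

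Inputs from section 2.5: d = 0.6, power 0.80, alpha 0.05 (taken as two-sided), 1:1 allocation.

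- Normal approximation: n = 2(1.960 + 0.842)²/0.6² = 43.6, so 44 per group.
- Two-sample t-test: 44.6, so 45 per group, with power 80.4% at n = 45. The stated 45 reproduces.
- 55 enrolled per arm leaves 45 if dropout is 1 - 45/55 = 18.2%, which fits the stated approximate 20%.

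**4. Illustration of what a shift could do**

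The documents give no bias size, so b = 0.1 and 0.2 SD toward HIIT are assumptions. With no true effect and n = 45 per arm, the t statistic has 88 degrees of freedom and non-centrality b x sqrt(n/2), where sqrt(22.5) = 4.743.

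| Assumed b | Share of d = 0.6 | Non-centrality | Two-sided rejection (nominal 5%) | Significant in favour of HIIT (nominal 2.5%) |
|---|---|---|---|---|
| 0.1 SD | 0.1/0.6 = 17% | 0.474 | 7.6% | 6.8% |
| 0.2 SD | 0.2/0.6 = 33% | 0.949 | 15.5% | 15.4% |

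The last two columns come from the same calculation; the final column counts only results that favour HIIT. The t-test stands in for the planned mixed model. Non-centrality grows with sqrt(n), so a larger trial would make the false rejection rate worse.

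**The case against.** The case on the other side is substantial.

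- **Team, not person.** A reader might infer that each HIIT patient is tested by their own trainer. Section 2.1 speaks only of staff affiliated with CSAM, and who tests whom may be settled in a fuller document. This stands: the overlap is certain for the team and only possible for the individual. It does not dispose of the point, because the article positively assigns both jobs to one team and does not separate them.
- **BRIEF-A completion.** Nothing says that a trainer sits with the patient or sees the answers, and private completion may already be the practice. This also stands, so the point asks for the condition to be stated and does not allege a breach.
- **The figures do not isolate this defect.** A reader might take 8-16% as the false-positive rate caused by the overlap. The documents do not support that. Participants know their allocation whoever collects the form, and the assumed shift cannot be divided between their expectation and the collector's influence.
- **The 24-to-0 count is narrow.** Both arms meet research staff for consent and baseline testing. Controls have physical activity four times a week within TAU, and Lade ATC sport therapists help to implement the HIIT sessions. The count describes supervised HIIT sessions only.
- **Protection beyond baseline.** A reader might infer that every post-randomization measure is equally open to bias. The computer-based tasks, the blood sampling and the treadmill criteria show otherwise.
- **Disclosure.** The lack of blinding is stated openly, so there is no contradiction. What remains is a design choice that could partly be avoided.

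One might also want a BRIEF-A difference called self-perceived function unless the computer-scored tests agree. That is not supported. The article already labels the instrument as self-report and holds that it "is considered more relevant for real-life situations than performance-oriented measures of executive functions", so divergence from performance tests would not in itself show bias. A requirement that the tests point the same way has no defined criterion.

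**Conclusion.** The point holds at team level. One unblinded team trains the HIIT arm and tests both arms, and the only stated safeguard ends at baseline. The asymmetry is up to 24 supervised sessions against none. It bears on the primary BRIEF-A comparison at week 8, on the MoCA and on the treadmill test; it bears much less on the computer-based tasks and the blood samples.

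The size of any collector-specific bias is unknown. The rejection rates of 7.6% and 15.5% rest on assumed shifts of 0.1 and 0.2 SD, no true effect, 45 evaluable patients per arm and two-sided alpha 0.05. They show how sensitive the test is to a modest shift from any source. They measure neither the harm done by overlapping roles nor the gain from separating them. The sample size is unaffected. The change is still worth making because it is cheap and bears on the primary conclusion.

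**What to change.** In sections 2.1 and 2.6, state that:

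1. After randomization, patients complete the BRIEF-A and the questionnaires privately, with no staff member who trained that patient present.
2. Within existing staff, the week-8 MoCA and treadmill test are run by a member who did not supervise that patient's HIIT sessions.
3. Participants know their allocation, so bias from their own expectations remains in the self-report outcomes; acknowledge this as a limitation.

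Items 1 and 3 are wording. Item 2 is a rota change with a small scheduling burden. It assumes that enough staff are available to split the roles; the article gives no headcount, though it mentions research staff at both CSAM and Lade ATC. A colleague from the same team may still know the allocation, so item 2 removes the training relationship but does not create blinding. The sample size, visits and analysis model stay as they are, and the interpretation of the primary result need not be made conditional on the computer-scored tests.
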